### Ethical and safety issues

The study has been approved by the Medical Ethics Committee of AMC (MEC 2012-02) and recruitment of the participants is in progress. The study is conducted according to the principles of the Declaration of Helsinki and in accordance with the Medical Research Involving Human Subjects Act. After participants have given informed consent, each participant receives an individual ID number to secure anonymity. The web-based questionnaires can only be completed by participants with this unique number and data from these questionnaires are collected on a secured server. In accordance with the act, the investigator will inform the participants and the accredited Medical Ethics Committee if anything occurs from which it appears that the disadvantages of participation may be significantly greater than was foreseen in the research proposal.

## Discussion

A multicenter RCT is proposed to support counselees in disclosing hereditary or familial cancer risk information to at-risk relatives. The aim of the intervention is to evaluate the effectiveness of an additional telephonic counseling session performed by psychosocial workers.

Genetic counselors rely on counselees to inform their relatives about their hereditary or familial cancer risk and the possibilities to reduce this risk. Therefore, it is important to maximize their ability to be a competent, motivated and confident informant while respecting their wish not to inform (some) relatives. The proposed intervention aims to support counselees in this difficult task and hopefully allow more at-risk relatives to make a well- informed decision. If effective, this intervention might lead to more relatives taking up genetic services and preventive screening and possibly reducing cancer morbidity and mortality in these affected families.

This is not the first intervention to enhance family communication about genetic testing and hereditary risk information [28-30]. However, to our knowledge, this is the first to 1) study the effectiveness of additional support using a randomized controlled design based on MI, 2) apply an intervention for mutation carriers and counselees with relatives with an increased risk to develop cancer, and 3) involve relatives in the study. Another strength is that the psychosocial workers delivering the intervention are specialized in genetics, are experts in working with cancer counselees, have well-developed communication skills, and are likely to have more time to deliver the intervention than clinical geneticists and/or genetic counselors.

Some limitations also need to be addressed. First, our patient sample is not truly representative for cancer counselees in general, since only index patients are invited to participate; this may affect the external validity. We did consider inviting all counselees who were advised to inform at-risk relatives, but rejected this idea because of the complexity of establishing which relatives have already attended genetic services and/or have already been informed by other relatives about their risk to develop cancer.

Second, similarity of the two study arms is not guaranteed since participants in the intervention arm receive more attention than the controls. Therefore, it is difficult to precisely define the effective components of the intervention. Also, a third study arm, comprising a condition with only a telephone call was considered to be too ambitious given the additional number participants required. However, to gain insight into the effective components of the intervention, we aim to compare the group of counselees who only needed the first phase of the intervention (that is, systematically exploring disclosure of genetic cancer information to at-risk relatives) with those who also received the second phase of the intervention (that is, building motivation, self-efficacy, brainstorming).

Moreover, pilot work revealed the complexity of gaining reliable insight into the counselees’ knowledge regarding which relatives to inform and what to tell relatives by asking them to complete questionnaires. Therefore, completion of the questionnaire after the intervention (T2) is done (in part) by telephone to ensure that the counselees understand the items correctly. This telephone call, performed by the researchers, might be seen as an intervention on its own, since counselees are asked about family communication in a systematic way. For that reason, the telephone call is scripted and standardized as far as possible.

Finally, studies in which relatives are invited to participate, including the present study, have some limitations. Medical-ethical regulations preclude geneticist/researchers from directly approaching the relatives of counselees. Therefore, we ask the participating counselees to invite their relatives to participate; this may cause some selection bias since only those relatives can be invited who have been correctly informed by the counselee. To prevent this bias, we use the pedigree of the participant, and for each individual relative, we systematically ask whether this relative may be invited or not.

This paper is the first of a series that will outline the development and testing of an intervention to enhance family communication about hereditary or familial cancer risks; here we describe the study protocol of the RCT. Additional papers will describe the development and psychometric properties of the outcome measures, pilot testing, and the outcomes of the trial.

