**Phase 1: exploring**		
Step 1	Agenda setting	Introducing the subject of family communication about hereditary or familial cancer risks and preventive measures. Explicitly ask the counselee if he/she is willing to discuss this issue.
Step 2	Exploring	Systematically exploring counselees’ current and planned pattern of informing relatives. Psychosocial workers investigate whether the counselee correctly knows which family members are at risk and which information should be provided to them.
*Evaluation*		*After the first phase the psychosocial worker verifies whether or not all at-risk relatives are informed thoroughly (thoroughly = at least the written advice in the summary letter). If the counselee has informed all at-risk relatives properly the psychosocial worker will end the counseling session. If not, the psychosocial worker will start phase 2.*

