### Randomization

ALEA (a software package to support online randomization in healthcare research) will be used to randomly allocate the participant to either the intervention or control group (allocation rate 1:1). This computer-based system ensures allocation concealment. In order to create equal comparison groups and prevent allocation bias, randomization will be stratified for three different groups (that is, conclusive versus inconclusive DNA test result) and whether or not the counselee has been diagnosed with cancer. To balance group sizes, random block randomization will be used with a maximum block size of 8 and block size factor 5.

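### The phase-1-only versus phase-2 comparison cannot show which component works, because the counselee's own disclosure decides the phase after randomisation

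*Protocol article*

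**What the plan says.** The Discussion of the protocol article concedes that the effective components are hard to identify because the intervention arm receives more attention, and that "a third study arm, comprising a condition with only a telephone call was considered to be too ambitious". It then offers a substitute. With the stated purpose "to gain insight into the effective components of the intervention", the authors write that "we aim to compare the group of counselees who only needed the first phase of the intervention" "with those who also received the second phase of the intervention (that is, building motivation, self-efficacy, brainstorming").

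Table 1 (Intervention elements) fixes how these groups arise. After phase 1, "the psychosocial worker verifies whether or not all at-risk relatives are informed thoroughly". The rule is then: "If the counselee has informed all at-risk relatives properly the psychosocial worker will end the counseling session". The other branch reads: "If not, the psychosocial worker will start phase 2".

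The Randomization section covers arm only: the software will "randomly allocate the participant to either the intervention or control group (allocation rate 1:1"). Phase is not randomised. Hypothesis 2 makes the number of relatives informed an outcome. The Background sorts the barriers to informing relatives into lack of knowledge, of motivation and of self-efficacy, and these three are the primary outcome domains.

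**The concern.** The comparison is given a causal purpose, but the two groups are formed after randomisation, inside one arm, by a variable that is itself an outcome of the trial. Counselees who stop after phase 1 are those judged to have completed the task that the intervention is meant to support. Those who continue have not. Any difference between them at T2 or T3 mixes this prior difference with whatever phase 2 does.

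Phase 2 holds the corrective information, the motivation and self-efficacy work and the brainstorming. A reader who takes the comparison at its stated purpose could conclude that this content is dispensable, or that it is the active ingredient, when the data support neither. The Discussion lists other limitations (attention, the T2 telephone call, selection of relatives) but not this one. It presents the comparison as a partial answer to the missing third arm.

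**Working it through.** The plan attaches no figure to this comparison, so there is none to reproduce. The 132 per group in Sample size concerns the randomised contrast and serves here only as the size of the intervention arm.

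**Inputs from the document**
- Stopping rule and its complement: Table 1.
- Unit of randomisation, arm only: Randomization.
- Correlation between measurements 0.7, arm size 132, assumed effects 0.5 and 0.2 (difference 0.3 SD): Sample size.

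**Assumed, because the document gives no value**
- T1 gap between the two phase groups: g = 0.5 SD.
- Share stopping after phase 1: 25%, 50%, 75%.
- Correlation r of the tendency to disclose with the T1 and T2 outcome: 0.1, 0.3, 0.5.

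**Step 1: overlap.** Let A = 1 if the worker finds all at-risk relatives properly informed, and A = 0 otherwise. Under Table 1, P(phase 2 | A = 1) = 0 and P(phase 2 | A = 0) = 1. No value of A contains both groups. Phase and A are the same variable, so no model can separate the effect of phase 2 from that of prior disclosure without extrapolation. This step needs no assumed figure.

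**Step 2: the T1 gap carries forward only through the T1 score; neither phase has an effect.**
- Raw T2 difference, phase-1-only minus phase-2: 0.7 × g = 0.7 × 0.5 = +0.35 SD.
- Change from T1: 0.35 − 0.50 = −0.15 SD, so phase 2 appears 0.15 SD better.
- Adjusted for T1: 0.35 − 0.7 × 0.5 = 0.

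The same data-generating assumption gives three answers, two of opposite sign.

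**Step 3: a lasting tendency to disclose acts on T1 and T2 alike; phase 2 has no effect.** The counselees with the strongest tendency form the phase-1-only group. The raw gap is r × φ(z) / [p(1 − p)], where p is the share stopping and z the cut-off. For p = 0.5 the multiplier is 0.399/0.25 = 1.60, which gives 0.16, 0.48 and 0.80 SD for r = 0.1, 0.3 and 0.5. A simulation with 400,000 draws agrees to about 0.01. Its ranges over the three shares, with rejection rates for a nominal 5% test in an arm of 132, are:

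| r | Raw T2 difference (SD) | Rejects | T1-adjusted (SD) | Rejects | Raw phase-2 minus phase-1-only if phase 2 truly adds 0.3 SD |
|---|---|---|---|---|---|
| 0.1 | 0.16 | 13–15% | 0.04–0.05 | 6–7% | +0.14 |
| 0.3 | 0.47–0.51 | 72–78% | 0.15–0.16 | 19–21% | −0.17 to −0.21 |
| 0.5 | 0.80–0.85 | 99–100% | 0.29–0.30 | 49–58% | −0.50 to −0.55 |

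Here the T1 gap equals the T2 gap, so a change-from-T1 comparison shows no bias, while T1 adjustment does.

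**Step 4: what follows.** T1 adjustment is unbiased in step 2 and biased in step 3; change from T1 is the reverse. Without control counselees of the same disclosure status, the phase comparison cannot tell which model applies. Choosing a different analysis therefore does not rescue the comparison.

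**The case against.** The strongest defence is the status of the comparison. It is one sentence among the limitations, worded as an aim to gain insight. It serves none of the three hypotheses and does not appear in Data analysis. No outcome, model or decision is tied to it. The text admits that components are hard to define, and its wording openly describes a need-based split. Details of adjustment may sit in an analysis plan that is not shown. All of this stands, and it limits the weight of the point. It does not answer it: the difficulty lies in the assignment rule, which the document states, and not in a modelling detail still to come.

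A reader might infer that phase-1-only counselees will almost surely do better, so that phase 2 would look useless or harmful whatever it truly does. The documents do not support that. They give no T1 gap, no share stopping and no correlation between disclosure and outcome. Data analysis specifies multilevel models over T1, T2 and T3, and Sample size defines the effect as a group/time interaction; in that form the step 2 figures favour phase 2 by 0.15 SD. Even in the raw comparison, a true gain of 0.3 SD at r = 0.1 would still show as +0.14 SD. Nor should 0.35 SD be set against the 0.3 SD of the sample size: the first is a raw T2 gap, the second a group/time effect between randomised arms.

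A reader might also take it as established that the groups differ in knowledge, motivation and self-efficacy. Table 1 fixes a difference in disclosure only. The Background makes the others probable, but Table 1 also names practical barriers, such as having no personal contact with a relative.

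**Conclusion.** The point holds as a limit on what may be concluded. The phase-1-only versus phase-2 comparison, carried out exactly as written, cannot show which component is effective. The split is made after randomisation on disclosure, and the rule leaves no overlap between the groups. That conclusion rests on Table 1, Randomization and the Discussion alone.

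The size of the bias cannot be derived from the documents, and its direction depends on the analysis. Under an assumed 0.5 SD gap at T1, the stated correlation of 0.7 and no phase effect, it is 0.35 SD in favour of phase-1-only on raw T2 scores and 0.15 SD in favour of phase 2 on change from T1. The randomised comparison of intervention with standard care is untouched. The wording should be corrected, but the trial's main conclusion does not depend on it.

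**What to change.** State that phase-1-only and phase-2 counselees will be described side by side (numbers, characteristics, outcomes), and that this supports no conclusion about effective components. This costs one sentence.

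Optionally, add a contrast that keeps the randomisation. Counselees' characteristics lists the number of relatives to be informed and the number informed as reported by the counselee, but gives no time point. The sponsor must confirm whether both are collected at T1. If they are, T1 disclosure status (all informed, yes or no) is fixed before randomisation in both arms, because the Recruitment section places the baseline questionnaire before allocation. The arm effect can then be estimated within each status with an arm-by-status interaction, labelled exploratory. If the counts are not collected at T1, this option falls away and the descriptive label stands alone.

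The added analysis has three downsides:
- The interaction will have low power.
- Self-reported T1 status only approximates the worker's later judgement, which is made with the pedigree at hand, and disclosure may change in between. Such misclassification does not break comparability between arms.
- It shows for whom the intervention works and does not isolate phase 2. Doing that would need randomisation to phase content, which this design does not have.

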### Counselees’ characteristics

Counselees’ characteristics include the following:

1. Demographic variables, which include age, gender, educational level, age of their children, and marital status.

2. Clinical characteristics, comprising genetic test result, cancer diagnosis, number of relatives to be informed, number of informed relatives (as reported by the counselee), age at which the counselee was first confronted with cancer in the family, and types of cancer in the family.

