### Sample size

For the primary research question we aim for a medium effect size. At baseline (T1), we assume no differences in primary outcomes between the intervention and control group. At T2 we expect to find a medium effect size. We assume this to be 0.5 for the intervention group and 0.2 for the control group, taking into account that the outcomes in the control group may be slightly affected by that fact that they are aware that the study focuses on informing their relatives; this effect is estimated to last until follow-up (T3).

Based on these assumptions, we require 132 patients in each group to have 80% power to detect an intervention effect (group/time interaction) that is significant at the 0.05 level (assuming a 0.7 correlation between measurements). In addition, we have a 99% chance to detect differences between measurement moments and a 46% chance to detect group differences overall.

Assuming a response rate of 50% and a 20% dropout, we need to approach 660 counselees. Preliminary work has shown that counselees are advised to inform (on average) 4.6 at-risk relatives. Assuming that counselees provide contact information for (on average) two relatives and that 50% of these relatives will complete the questionnaire, it is estimated that we will have data on 264 relatives.

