### Data analysis

All analyses will be based on the intention-to-treat principle. Assuming random dropout, incomplete data will be imputed using data of the control group, that is, standard care.

*Hypothesis 1:* Multilevel analysis will be used to investigate whether the intervention increases counselees’ knowledge, motivation and self-efficacy as compared with the control group. Effects of the intervention will be investigated on each of the seven outcome variables separately. The three moments of measurement (T1, T2, T3) will be treated as nested within counselees.

*Hypothesis 2:* Multilevel analysis will also be used to investigate whether the intervention increases: the number of correctly informed relatives; relatives’ knowledge about hereditary/familial cancer and preventive measures; and relatives’ intention to engage in genetic counseling. For this, the relatives will be treated as nested within counselees and counselees will be treated as nested within physicians.

*Hypothesis 3:* To investigate how counselees and psychosocial workers evaluate the intervention, descriptives and frequencies will be calculated to present counselees’ and psychosocial workers’ evaluation of the intervention.

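### Relatives' knowledge and intention (Hypothesis 2) are compared after a selection that the intervention is meant to change; the pedigree records this selection but does not prevent it, and the outcome free of it is not listed as an outcome

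*Protocol article*

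**What the plan says.** Counselees are randomised after the T1 questionnaire (Recruitment and informed consent, Counselees). Relatives enter at T3, four months after T1, by the counselee's invitation, and return a questionnaire if they wish (Participants, Relatives; Recruitment and informed consent, Relatives). Direct approach by researchers is ruled out by medical-ethical regulation.

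The Discussion concedes a possible selection bias because "only those relatives can be invited who have been correctly informed by the counselee". It continues: "To prevent this bias, we use the pedigree of the participant", and adds that the counselee is asked, relative by relative, whether an invitation may be made.

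Hypothesis 2 (Background) has three parts: more at-risk relatives informed, more knowledge among relatives, and stronger intention among informed relatives. The Data analysis section compares all three between arms by multilevel models. There the first part becomes "the number of correctly informed relatives". The Secondary outcome measures section lists relatives' knowledge, intention and evaluation, but not the number informed. That quantity appears only under Counselees' characteristics, among the clinical variables, as "number of informed relatives (as reported by the counselee").

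**The concern.** Being informed is the behaviour that the session tries to change. If the intervention works as Hypothesis 2 predicts, the informed relatives in the two arms are different kinds of people, and only they can supply a questionnaire. The counselee's permission and the relative's willingness then act as further filters, also after randomisation. A difference in mean knowledge or intention among responders could reflect who got in, what the session did, or both.

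If the protocol is taken at its word that the bias is prevented, such a difference would be reported as an effect of the intervention. An absence of difference would be read as a failure to reach relatives. Neither reading is supported. The quantity that could answer the disclosure question without relatives having to pass these filters is not in the outcome lists and carries two labels.

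**Working it through.** **Does the pedigree step remove the selection?** The filters, in order, are:

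1. The relative was correctly informed (Discussion). Hypothesis 2 predicts a difference between arms here.
2. The counselee agrees to involve relatives and permits this one to be invited (Recruitment and informed consent; Discussion).
3. The relative returns the questionnaire (Recruitment and informed consent).

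The pedigree fixes who is eligible, and the per-relative question records who is withheld. Neither brings in an uninformed or withheld relative. The step yields a denominator and a count of exclusions; the set of relatives analysed is unchanged.

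**The plan's own figure.** The Sample size section assumes 264 counselees, two relatives each and 50% response: 264 × 2 × 0.50 = 264 relatives, as stated. The same section says "counselees are advised to inform (on average) 4.6 at-risk relatives". That implies 264 × 4.6 = 1,214 relatives to be informed, of whom 2/4.6 = 43% would be invited and 264/1,214 = 22% analysed. The 22% is coverage pooled over both arms.

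**What selection alone can do (illustration).** The documents give no informed rates, so every input here is assumed. Let pC and pI be the shares informed in the control and intervention arms. Suppose that everyone informed under standard care would also be informed under the intervention, that no relative's knowledge is truly affected, and that the extra informed relatives score d SD below the others. The spurious difference is then

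−[(pI − pC)/pI] × d.

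For 60% against 75% and d = 0.5: (0.75 − 0.60)/0.75 = 0.20, and 0.20 × 0.5 = 0.10 SD lower in the intervention arm. Below, the percentage in brackets is the chance of a significant result at two-sided 0.05, taking 132 independent relatives per arm (standard error √(2/132) = 0.123 SD).

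| Informed, control → intervention | Extra share | d = 0.3 | d = 0.5 | d = 0.8 |
|---|---|---|---|---|
| 60% → 70% | 14.3% | −0.043 (6.4%) | −0.071 (8.9%) | −0.114 (15.3%) |
| 60% → 75% | 20.0% | −0.060 (7.8%) | −0.100 (12.8%) | −0.160 (25.5%) |
| 60% → 80% | 25.0% | −0.075 (9.3%) | −0.125 (17.4%) | −0.200 (36.9%) |
| 50% → 70% | 28.6% | −0.086 (10.7%) | −0.143 (21.3%) | −0.229 (45.9%) |

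The signs flip if the extra relatives score higher. Selection by permission and response is left out and could add to these values or offset them.

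**Can the number informed carry Hypothesis 2?** With 132 counselees per arm, the smallest detectable difference in a counselee-level proportion (80% power, two-sided 0.05) is (1.96 + 0.84) × √(2/132) = 0.34 SD. On the proportion scale, the design effect is 1 + (4.6 − 1) × ICC and the effective number per arm is 132 × 4.6 divided by it. For assumed ICCs of 0.1, 0.3 and 0.5 this gives 446, 292 and 217. Power for 60% against 70% is 88%, 72% and 59%; for 60% against 75% it is 99.8%, 97% and 92%. The outcome is workable at the planned size.

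**Is that outcome fixed consistently?** Set side by side: Hypothesis 2 says informed; Counselees' characteristics says informed, by counselee report; Data analysis says correctly informed, without a definition. The nearest criterion is in Table 1 (the written advice in the summary letter as a minimum), but psychosocial workers apply it during the session, so it exists in one arm only.

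**The case against.** The protocol names the selection openly, and its cause is a regulation that the investigators cannot change. The intention part of Hypothesis 2 is worded for informed relatives, so its population is declared as conditional. The number informed is named in the hypothesis and has a between-arm analysis, so its absence from the outcome list could be called a missing line. The trial is powered on Hypothesis 1, which relatives' selection does not touch.

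Much of this stands and limits the point:

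- A reader might infer that Hypothesis 2 cannot be answered at all. Its first part can be, from counselees' reports.
- A reader might infer that the intervention arm must look worse, because Table 1 directs brainstorming at relatives who are harder to approach. Nothing in the document says that such relatives know or intend less once informed.
- The 22% might be read as evidence of differential bias. It is not: it is pooled over arms, and its denominator ignores the age and language limits on eligible relatives.
- The Data analysis section does not say that the number informed is taken from relatives' questionnaires, so that defect should not be charged to it.

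What does not stand is the claim of prevention. Disclosing a bias and declaring a conditional population do not turn a comparison conditioned on a consequence of treatment into a randomised one.

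**Conclusion.** The point holds in this form. The comparison of relatives' knowledge and intention between arms rests on a selection made after randomisation, on a variable that the trial's own hypothesis expects to differ by arm. The statement that the pedigree prevents the resulting bias is wrong. Direction and size are unknown; the range of 0.04 to 0.23 SD, with false-positive rates of 6% to 46% in place of 5%, holds only under the assumed rates and score gaps shown.

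The counselee-reported number informed is free of selection of relatives. It is not free of counselee dropout, nor of self-report bias: counselees in the intervention arm know that they had a session on disclosure, even though they are masked to the exact study objective. It is treated as a Hypothesis 2 endpoint but is missing from the outcome lists and inconsistently labelled.

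This should be corrected, but it is not critical to the trial, since Hypothesis 1 and the powered primary outcomes are unaffected.

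**What to change.** 1. List as a defined secondary outcome, and as the lead outcome for Hypothesis 2, the number or proportion of relatives to be informed whom the counselee reports as informed at T3. Record it before the invitation packs are handed over, since inviting a relative may itself prompt disclosure. Analyse it over all randomised counselees, using the two counts already named under Counselees' characteristics (relatives to be informed, relatives informed). Use a relative-level model only if informed status is recorded for each relative. The article shows a per-relative question on permission to invite, not on having been informed, so this may need an added T3 item.
2. Use one term throughout. If correctly informed is meant, define it in a way that can be measured alike in both arms.
3. Report by arm the numbers of relatives eligible, informed, permitted, invited and responding.
4. Interpret relatives' knowledge and intention as conditional on being informed and responding, not as a randomised effect. An analysis that scores uninformed relatives as not knowing is at most a sensitivity analysis: it needs stated assumptions for informed relatives who did not respond, and others may have told those whom the counselee did not.
5. Replace the claim of prevention in the Discussion with a statement that the pedigree quantifies the selection and that the bias remains.

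The cost is mainly wording in the outcome, analysis and Discussion sections. Recruitment is in progress, so the changes are best made before outcome data are analysed. The price is that the lead Hypothesis 2 outcome rests on self-report by counselees who know whether they had the session.
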